## Abstract

**Background:**

Vitamin D deficiency has been associated with hypertensive disorders in pregnancy (HDP). The risk of developing HDP was reported to be further augmented among individuals with a vitamin D receptor (VDR) genetic variant. However, the reported roles of *VDR* variants in hypertensive disorders are inconsistent among different populations. Given the relatively higher incidence of vitamin D deficiency among Malaysian pregnant women and the high incidence of HDP in this population, we hypothesize that there may be associations between the risk of vitamin D deficiency and HDP with VDR genetic variants.

**Objective:**

This paper outlines the protocol for a study to determine the association of vitamin D status and *VDR* sequence variants among Malaysian pregnant women with HDP.

**Methods:**

This prospective study consists of two phases. The first phase is a cross-sectional study that will entail gathering medical records, a questionnaire survey, and laboratory testing for vitamin D status, with a planned recruitment of 414 pregnant women. The questionnaire will be utilized to assess the risk factors for vitamin D deficiency. The vitamin D status will be obtained from measurement of the vitamin D (25-hydroxyvitamin D_3_) level in the blood. The second phase is a case-control study involving a Malay ethnic cohort with vitamin D deficiency. Participants will be divided into two groups with and without HDP (n=150 per group). Genomic DNA will be extracted from the peripheral blood monocytes of participants using the Qiagen DNA blood kit, and *VDR* sequence variants will be determined using polymerase chain reaction–high-resolution melting (PCR-HRM) analysis. Sanger sequencing will then be used to sequence randomly selected samples corresponding to each identified variant to validate our PCR-HRM results. The *VDR* genotype and mutation frequencies of *BsmI*, *ApaI, TaqI,* and *FokI* will be statistically analyzed to evaluate their relationships with developing HDP.

**Results:**

As of December 2023, 340 subjects have been recruited for the phase 1 study, 63% of whom were determined to have vitamin D deficiency. In the phase 2 study, 50 and 22 subjects have been recruited from the control and case groups, respectively. Recruitment is expected to be completed by March 2024 and all analyses should be completed by August 2024.

**Conclusions:**

The outcome of the study will identify the nonmodifiable genetic components contributing to developing vitamin D deficiency leading to HDP. This will in turn enable gaining a better understanding of the contribution of genetic variability to the development of HDP, thus providing more evidence for a need of customized vitamin D supplementation during pregnancy according to the individual variability in the response to vitamin D intake.

**Trial Registration:**

ClinicalTrials.gov NCT05659173; https://clinicaltrials.gov/study/NCT05659173

**International Registered Report Identifier (IRRID):**

DERR1-10.2196/53722

## Introduction

Vitamin D deficiency is a global health issue affecting an estimated 1 billion people worldwide across all ethnicities and age groups [1]. Thus, vitamin D deficiency has become a pandemic despite the availability of sunlight in Asia, Africa, the Middle East, and Latin America. The most vulnerable populations at risk of vitamin D deficiency are pregnant women and their fetuses. Several studies have linked low vitamin D status with a higher risk of adverse short- and long-term health outcomes. In addition, risk factors such as dietary habits, cultural and religious practices such as wearing dark veils covering nearly all body parts that discourage sun exposure, and lack of government regulations for vitamin D fortification of foods further worsen the condition [2,3]

Hypertensive disorders in pregnancy (HDP) account for approximately 14% of all causes of maternal mortality globally. The spectrum of HDP includes gestational hypertension (GH); preeclampsia; eclampsia; and hemolysis, elevated liver enzymes, and low platelets (HELLP) syndrome. Preeclampsia is a complication of 2%-8% of all pregnancies worldwide, contributing to 16%, 9%, and 1.6%-2.5% maternal deaths globally, in Asia and Africa, and in Malaysia, respectively [4,5]. HDP is one of several disorders associated with vitamin D deficiency [6]. Vitamin D exerts its effect through the nuclear vitamin D receptor (VDR), and several single-nucleotide variants (SNVs; formerly single-nucleotide polymorphisms or SNPs) occur on the VDR gene, such as *BsmI, ApaI, TaqI*, and *FokI* SNVs. The *BsmI* and *FokI* variants of *VDR* have been reported to affect vitamin D binding and are associated with an increased risk of HDP [7].

In pregnant women, maternal 25-hydroxyvitamin D (25(OH)D) can freely cross the human placenta that expresses VDR and the enzyme CYP27B1, which converts 25(OH)D to its biologically active form 1,25-dihydroxycholecalciferol [8]. VDR is a protein comprising two functional domains (the N-terminal dual zinc finger DNA-binding domain and the C-terminal ligand-binding activity domain) and a linking region [9,10]. The gene encoding VDR is located on chromosome 12 (12q12-14) [11,12]. Several SNVs in the VDR gene have been associated with metabolic disorders and vitamin D deficiency to date, including rs1544410 (*BsmI*), rs7975232 (*ApaI*), and rs731236 (*TaqI*) [12].

Sequence variants in the VDR gene are associated with the dysregulation of metabolic biomarkers such as anthropometric parameters related to insulin resistance, obesity, and cardiovascular diseases, along with atherogenic lipid abnormalities in different populations [12,13]. Such metabolic dysregulation ultimately translates into complications in pregnancy with adverse health consequences for both the pregnant woman and the fetus. Vitamin D exerts its effect through the nuclear VDR. The *TaqI* variant, located at the 3′ untranslated region of the VDR gene, has been shown to affect mRNA stability and VDR expression in tissues. An SNV in *FokI* located near the promoter region causes altered VDR activity due to the change in the amino acid sequence of the protein [14]. A *FokI* variant of the VDR gene is also associated with upregulation of angiotensin II type I receptor and renin gene transcription, leading to hypertension [15]. A variant *BsmI* allele also influences *VDR* mRNA stability, resulting in a reduction in the amount of VDR protein produced in the tissues [16].

Accumulating evidence suggests that genetic variability involving variants of specific maternal susceptibility genes, such as those in the VDR gene, play vital roles in the pathogenesis of HDP [6]. An unfavorable *VDR* genetic background can significantly decrease the effectiveness of vitamin D action, thereby contributing to the development of HDP [6,17].

Moreover, the presence of a *VDR* sequence variant constitutes an important factor contributing to the individual susceptibility to the biological effects of vitamin D. HDP may be apparent in some pregnant women, whereas others present with a relatively milder sequela. Considering the influence of genetic variability and the roles of *BsmI, ApaI, TaqI*, and *FokI* variants in the etiopathogenesis of HDP, we aim to explore the possible association between the frequencies of these genetic variants and the incidence of HDP in Malaysian pregnant women. Given the estimated high prevalence of vitamin D deficiency among Malaysian pregnant women, we hypothesized that there are sequence variants in the *BsmI* and *FokI* VDR gene fragments (as the most common genotypes associated with HDP) of Malaysian pregnant women with vitamin D deficiency. We further explored associations with *ApaI* and *TaqI* variants given the relative lack of previous research on the potential associations of these genotypes with HDP.

## Methods

### Objectives

The objectives of this prospective study are to (1) determine the prevalence of vitamin D deficiency and associated risk factors among Malaysian pregnant women; (2) determine the frequencies of *BsmI*, *ApaI, TaqI,* and *FokI* genotypes among Malay pregnant women with vitamin D deficiency and HDP; (3) understand and associate the distributions of *VDR* genotype and allele frequencies in relation to vitamin D deficiency among Malay pregnant women; and (4) identify mutations in the *BsmI*, *ApaI, TaqI,* and *FokI* VDR gene fragments among Malay pregnant women with HDP.

This study is divided into two phases. Phase 1 is a cross-sectional study involving Malaysian pregnant women to achieve objective 1, whereas phase 2 is a case-control study among Malay pregnant women to achieve objectives 2, 3, and 4.

### Settings

This study will be carried out at Hospital Sultan Abdul Aziz Shah (HSAAS), a tertiary university hospital in Selangor, Malaysia. The hospital provides a range of health care services to the neighboring community and serves as the teaching hospital for the Faculty of Medicine and Health Sciences, Universiti Putra Malaysia. All pregnant women attending the Obstetrics and Gynaecology Department of HSAAS who fulfill the inclusion and exclusion criteria will be recruited between November 1, 2022, and March 31, 2024. A systematic random sampling method will be used to recruit the study participants for both the cross-sectional and case-control studies.

### Cross-Sectional Study (Phase 1)

#### Participants and Data

To achieve objective 1, Malaysian pregnant women, at any stage of gestation, with a singleton viable pregnancy at the time of recruitment and who are literate in the English or Malay language will be recruited. Women with a multiple pregnancy and on vitamin D supplementation are excluded. The gestation stage will be determined from the first day of the last menstrual cycle or based on measurement of the fetal crown-rump length determined on an ultrasound scan. Pregnant women taking vitamin D supplements or those who have been diagnosed with chronic diseases that are known to affect vitamin D levels, such as autoimmune disease and cancer, are excluded from the study.

Clinical, sociodemographic, dietary intake, and anthropometric (height, weight, and BMI) data will be collected using a pro forma. The prepregnancy BMI (kg/m^2^) will be calculated by dividing the weight (kg) by the square of the height (m^2^). Weight will be determined from prepregnancy body weight recall or obtained from the woman’s antenatal booking record along with the measured height. Participants will then be interviewed by a single trained interviewer to answer a validated questionnaire to determine their risk factors associated with vitamin D deficiency.

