### Data Analysis Plan

Data obtained from the study will be analyzed using SPSS version 27.0 (IBM Corp). Data entered will be checked for missing or suspicious values. These will subsequently be verified with the participants or omitted as missing values. Descriptive analysis will be used to summarize the sociodemographic data, anthropometric data, clinical data, vitamin D dietary intake, sun exposure, and physical activity. The prevalence of vitamin D deficiency will be expressed in frequency and percentage. The association with sociodemographic data will be analyzed using the *χ*^2^ test, independent *t* test, and ANOVA where applicable.

We will report the comparative prevalence of *BsmI*, *ApaI, TaqI,* and *FokI*
*VDR* genotypes among Malay pregnant women with vitamin D deficiency with and without HDP. Similarly, the distributions of *VDR* genotype and allele frequencies according to vitamin D deficiency among Malay pregnant women will be reported as a descriptive analysis. Any mutations found in the *BsmI*, *ApaI, TaqI,* and *FokI* VDR gene fragments among Malay pregnant women with HDP will also be described. The associations of vitamin D status, associated risk factors, and VDR genetic variants with HDP will be determined using multivariate logistic regression analysis. The level of significance will be considered at a threshold of *P*≤.05 at the 95% CI.

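### The rule for prepregnancy BMI accepts a booking weight taken at any gestation, so it can count pregnancy weight gain as prepregnancy weight (minor)

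*Protocol article*

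**What the plan says.** All the relevant rules stand in the protocol article, under Cross-Sectional Study (Phase 1), Participants and Data, and under Data Analysis Plan.

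- **Variable.** Prepregnancy BMI is defined as weight over height squared.
- **Weight source.** "Weight will be determined from prepregnancy body weight recall or obtained from the woman’s antenatal booking record along with the measured height". The two sources are joined by a plain *or*. The text gives no latest gestation for a booking weight and does not ask for the source to be recorded.
- **Who is recruited.** "Malaysian pregnant women, at any stage of gestation, with a singleton viable pregnancy at the time of recruitment". No eligibility criterion concerns when a woman booked.
- **Collection.** "Clinical, sociodemographic, dietary intake, and anthropometric (height, weight, and BMI) data will be collected using a pro forma". The women are also interviewed by one trained interviewer.
- **Use.** The first objective covers the prevalence of vitamin D deficiency and its risk factors. The Data Analysis Plan summarises anthropometric data descriptively, then states: "The associations of vitamin D status, associated risk factors, and VDR genetic variants with HDP will be determined using multivariate logistic regression analysis". BMI is not named in that sentence.

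**The concern.** Recall aims at weight before conception. A booking weight, read naturally, is measured at a visit during pregnancy and contains whatever has been gained by then. If either may be used, two women with the same prepregnancy weight can receive different prepregnancy BMIs because one booked later, or because one could not recall her weight.

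A gain contained in the weight pushes BMI upward, so the error does not average out around the true value. What is at stake is the reading of BMI as a risk factor in Phase 1. If the error is unrelated to vitamin D status, a comparison of mean BMI by status loses precision, and a regression slope on BMI is diluted. If time of booking, or ability to recall weight, differs by vitamin D status, the comparison itself is biased, in a direction the article does not let us predict.

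**Working it through.** The plan states no figure on this point, so there is none to reproduce. The check is the size of the error in the derived variable.

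**Inputs**

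- Formula for BMI: from the article, weight (kg) / height (m)².
- Weight gained by booking, *g*: not given. Assumed 0, 2, 5 or 8 kg. Zero stands for early booking or use of recall (taken as accurate).
- Height, *h*: not given. Assumed 1.55 m, with a range of 1.50 to 1.60 m.
- Share of women whose BMI rests on a booking weight that contains gain, *f*: not given, so left as a symbol.

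**Error for one woman**

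BMI error = (W + g)/h² − W/h² = g/h², which does not depend on her true weight W. At 1.55 m, h² = 2.4025.

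| Assumed gain by booking | Error at 1.55 m (kg/m2) | At 1.60 m to 1.50 m (kg/m2) |
|---|---|---|
| 0 kg | 0 | 0 |
| 2 kg | 2/2.4025 = 0.83 | 0.8 to 0.9 |
| 5 kg | 5/2.4025 = 2.08 | 2.0 to 2.2 |
| 8 kg | 8/2.4025 = 3.33 | 3.1 to 3.6 |

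The range uses h² = 2.56 at 1.60 m and h² = 2.25 at 1.50 m.

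**Error in a group**

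If affected women share the same *g* and *h*, mean BMI is overstated by f × g/h². This runs from 0 when no woman is affected to the full table value when all are. In a comparison of mean BMI between deficient and non-deficient women, the bias is (f₁ − f₀) × g/h², where f₁ and f₀ are the affected shares in the two groups. It vanishes when the shares are equal. The article gives neither share.

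**What depends on BMI**

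- Prevalence of deficiency is a proportion based on measured 25(OH)D. BMI does not enter.
- The unadjusted comparison of genotype frequencies between women with and without HDP does not use BMI.
- Risk factors for deficiency in Phase 1: BMI is collected in that phase and is a candidate.
- The logistic model for HDP: BMI enters only if it is counted among the associated risk factors.

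**The case against.** The strongest reply is that a journal article condenses a longer protocol. The pro forma is not shown and may set an order between the sources. Recall is named first, so booking weight may be only a fallback. The booking record might itself hold a reported prepregnancy weight. Recruitment at any gestation says nothing about when women booked.

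Much of this stands. The lack of a stated order is not itself the point, and no one can say from the article that any woman's BMI is in fact wrong. What remains is the rule that is stated: it admits a booking weight without limit under a prepregnancy label, nothing elsewhere in the article narrows it, and no criterion excludes late bookers.

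A reader might infer three larger harms that the article does not support:

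- **Different error in cases and controls because of fluid gain in HDP.** This needs late booking, use of the booking weight, and fluid gain already present at booking. Nothing in the article establishes that combination.
- **Many women moving up a BMI category.** The article gives no BMI categories, no BMI distribution and no distribution of gestation at booking.
- **Confounding of the genotype comparison.** Germline genotype is fixed before BMI, and the Data Analysis Plan names BMI in no model. Phase 2 also recruits only vitamin D-deficient women, so little contrast in vitamin D status is left there for BMI to confound.

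It is also fair to say that recall has its own error. The article already lists recall bias as a limitation for its food-frequency items.

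**Conclusion.** The point holds in a limited, conditional form. As written, the rule can overstate prepregnancy BMI for a woman who booked after gaining weight and whose booking weight is used. The size is negligible for early booking and about 2 to 3 kg/m2 for assumed gains of 5 to 8 kg. Both figures rest on assumed gains and heights, and on the booking record holding a weight measured at the visit. The share of women affected is unknown.

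The consequence is confined to BMI as a candidate risk factor in Phase 1 and to any later model that includes it. Severity is minor, but the correction is cheap enough to be worth making.

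**What to change.** Change the source rule in the Phase 1 Participants and Data section along these lines:

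> Every participant will be asked at interview for her recalled prepregnancy weight. A booking weight will be accepted as a proxy only if it was taken in the first trimester. A later booking weight will not be used for prepregnancy BMI. The weight source and the gestation at booking will be recorded.

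The rule should also say in advance which weight is used when both are available. Either order is defensible if the source is recorded. The first-trimester limit assumes that little weight has been gained by then. The article has no data on this, so the team should confirm the limit for its own population.

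Record the source on the pro forma, since it is a study decision and will not be in the antenatal record. Take gestation at booking from the antenatal record. Do the same, where recoverable, for women already enrolled (340 in Phase 1 by December 2023). Repeat any analysis that uses BMI by weight source.

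The cost is a short change of text, two data fields, one sensitivity analysis and back-checking of enrolled women. The downside is some missing BMI values among late bookers who cannot recall their weight, and some reliance on recall. The number with missing BMI should be reported.

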#### Validation of the Questionnaire

The questionnaire was adapted from the studies of Syed Nor et al [18], Jamil et al [19], and Humayun et al [20] (see Multimedia Appendix 1). Permission was obtained from all authors to adopt their questionnaires and translate them into the Malay language. The translation will be performed by two English-Malay-English translators before the validation test. A pilot test will be carried out among 40 pregnant women (approximately 10% of the calculated sample size) to assess the questionnaire’s clarity of meaning, appropriateness of the words used, and its cultural acceptance. Participants recruited for the pilot testing will not be included in the study. The reliability will be measured by calculating the internal consistency and assessing the associations among questions. A Cronbach α value of at least 0.7 indicates good internal consistency of the questionnaire [21].

In addition, the content validity index (CVI) will be calculated to measure the validity of the questionnaire where the relevancy of questions will be assessed by three experts in the field. The item-level CVI will be calculated by assessing each question’s validity, in which a score above 0.78 is considered acceptable [22]. The overall validity of the questionnaire will also be measured by calculating the scale-level CVI, in which a score above 0.9 is considered good [22].

#### Sampling Process

Approximately 5 milliliters of blood will be withdrawn and dispensed into a plain blood bottle for the measurement of 25(OH)D_3_ using an electrochemiluminescence immunoassay (Elecsys Vitamin D Total III assay). This assay kit includes a vitamin D–binding protein (VDBP) labeled with a ruthenium complex as the capture protein to bind 25(OH)D_3_ and 25(OH)D_2_. Cross‑reactivity to 24,25(OH)D is blocked by a specific monoclonal antibody.

The sample will first be incubated with pretreatment reagents 1 and 2, where bound 25(OH)D is released from the VDBP. Subsequently, the pretreated sample is incubated with the ruthenium-labeled VDBP to form a complex between 25(OH)D and the ruthenylated VDBP. A specific unlabeled antibody binds to the 24,25(OH)D present in the sample and inhibits cross-reactivity to this vitamin D metabolite. During the third incubation, streptavidin-coated microparticles and 25(OH)D labeled with biotin are added. Unbound ruthenylated-labeled VDBPs become occupied, and a complex consisting of the ruthenylated VDBP and the biotinylated 25(OH)D is formed, which finally binds to the solid phase via the interaction of biotin and streptavidin.

The reaction mixture is aspirated into the measuring cell where the microparticles are magnetically captured onto the surface of the electrode. Unbound substances are then removed with ProCell/ProCell M. Application of a specific voltage to the electrode then induces chemiluminescent emission, which is measured by a photomultiplier. The results are determined via a calibration curve that is specifically generated by a 2‑point calibration process and compared to a master curve provided via the reagent barcode or e‑barcode.

#### Quality Control

Per-run control sera (deficient, insufficient, and normal) will be used for sample analysis. All laboratory analytical protocols will be performed with strict adherence to the quality control measures.

#### Classification of Vitamin D Status

The results will be further classified according to vitamin D status as deficient (˂30 nmol/L), insufficient (30-50 nmol/L), and normal (≥50 nmol/L), using the 2011 classification guidelines of the Institute of Medicine [23].

### Case-Control Study (Phase 2)

#### Participants and Data

For the second phase of the study, we chose to focus on the Malay ethnic group, who make up the majority of the Malaysian population. Pregnant women of Malay ethnicity who are classified in the vitamin D deficiency group in phase 1 of the study will be recruited for phase 2. Those with a nonviable pregnancy or those who received a diagnosis of chronic hypertension prior to the current pregnancy will be excluded. The remaining participants will then be divided into two groups: those with HDP (GH, preeclampsia, eclampsia, HELLP syndrome) and those with blood pressure in the normal range.

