### Sample Size Estimation

#### Total Sample Size

A total of 414 pregnant women will be recruited for the cross-sectional study (phase 1) to determine the prevalence of vitamin D deficiency and associated risk factors (objective 1). For phase 2, a total of 150 Malaysian pregnant women with HDP will be recruited as the case group and 150 normotensive Malaysian pregnant women with vitamin D deficiency will be recruited as controls.

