**(1)**

where n is the minimum sample size, Z is the level of significance at the 95% CI (1.96), p is the prevalence rate, q = 1 − p, and d is the tolerable margin of error (5%).

According to Woon et al [26], the prevalence of vitamin D deficiency among Malaysian pregnant women is 42.6%. Applying equation 1, the sample size is calculated as follows:

n = (1.96)^2^ × 0.426 × (1 – 0.426)/(0.05)^2^

n **=** (3.8416 × 0.426 × 0.574)/0.0025 = 376

Therefore, the minimum sample size required for the cross-sectional study after addition of a 10% attrition rate is approximately 414 Malaysian pregnant women.

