## Results

As of December 2023, a total of 340 subjects have been recruited for the phase 1 study. Preliminary analysis showed that 63% of the participants were vitamin D–deficient. Other analyses are pending. For the phase 2 study, 50 control subjects and 22 case subjects have been recruited to date. We are expecting to complete the recruitment by March 2024 and to complete all laboratory and questionnaire analyses by August 2024.

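### The 150 hypertensive cases are nested in a phase 1 sample of 414 that cannot supply them without targeted recruitment, and any such targeting would bias the phase 1 prevalence upward

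*Protocol article*

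**What the plan says.** All references are to the protocol article.

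- **Case-Control Study (Phase 2), Participants and Data.** Malay women "classified in the vitamin D deficiency group in phase 1 of the study will be recruited for phase 2". After exclusions for nonviable pregnancy and chronic hypertension, "The remaining participants will then be divided into two groups", one with HDP and one with normal blood pressure. Read as written, every case and every control is a member of phase 1.
- **Total Sample Size.** Phase 1 is 414 women. The case target reads: "a total of 150 Malaysian pregnant women with HDP will be recruited as the case group". The control group has the same size and consists of deficient women with normal blood pressure. This section does not repeat the phase 1 condition, and it attaches deficiency only to the controls.
- **Settings** gives systematic random sampling for both phases. **Strengths and Limitations** says that convenience sampling is used and leaves systematic random sampling to future studies.
- **Results**, as of December 2023: 340 women in phase 1, 63% of them deficient. "For the phase 2 study, 50 control subjects and 22 case subjects have been recruited to date". Recruitment was due to end in March 2024.
- **Sample size sections.** Phase 1 rests on a 5-point margin of error. Phase 2 uses deficiency of 21% in gestational hypertension and 11% in normotensive pregnancy.

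**The concern.** Phase 1 has two jobs. It is the prevalence sample for Objective 1, which needs women to enter without regard to blood pressure. On the phase 2 wording it is also the pool from which all cases come, and the case target is far above what such a sample yields. The two jobs pull against each other: the natural way to raise the case count at a single hospital is to approach women because they have HDP, and under the stated nesting those women would first have to be tested and classified in phase 1. No rule in the article keeps them out of the prevalence count.

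The study's premise is that HDP and deficiency go together. A phase 1 sample enriched for HDP would then overstate deficiency, and the prevalence would depend partly on how hard cases were pursued. The confidence interval would not reveal this, because it reflects sampling error only.

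**Working it through.** **1. The plan's own phase 1 figure.** n = 1.96² × 0.426 × 0.574 / 0.05² = 375.7, rounded to 376; 376 × 1.10 = 413.6, so 414 reproduces. It was sized for prevalence alone.

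**2. Share of phase 1 that the cases require.** 150/414 = 36.2%. This is a floor, reached only if every woman with HDP is deficient.

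**3. Projected supply of cases.** This assumes that the 22 cases are among the 340.
- Interim rate: 22/340 = 6.5%.
- Projected to 414: 0.0647 × 414 ≈ 27 cases.
- Women needed for 150 cases at this rate: 150 × 340/22 ≈ 2,318.
- Position in December 2023: 150 − 22 = 128 cases missing, 414 − 340 = 74 phase 1 places left.

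**4. Total supply for phase 2.** Phase 2 needs 300 deficient women, 300/414 = 72.5%. At 42.6% deficient, 414 women give 176; at 63% they give 261. Both fall short, before the Malay-only restriction.

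**5. Model for the size of the bias.**
- Odds ratio from the article's 21% and 11%: (0.21 × 0.89)/(0.79 × 0.11) = 2.15, assumed to carry over to the local level of deficiency.
- Deficient women so far: 0.63 × 340 = 214.2.
- The 22 cases are taken as all the deficient women with HDP so far. Solving for the two prevalences that fit 63% overall gives 61.7% deficient without HDP and 77.6% with HDP. That implies 22/0.776 ≈ 28 women with HDP, 28/340 ≈ 8% of phase 1.

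**6. Scenarios on the odds-ratio scale.**
- *All 74 remaining places go to women with HDP.* HDP share (28 + 74)/414 ≈ 25%. Prevalence (214.2 + 74 × 0.776)/414 = 65.6%, a shift of **+2.6 points**. Cases reach only 22 + 57 ≈ 79.
- *Phase 1 is extended with women with HDP until 150 cases.* This needs 128/0.776 ≈ 165 more women, about 505 in all, 38% with HDP. Prevalence (214.2 + 128)/505 = 67.8%, a shift of **+4.8 points**.

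**7. The same scenarios on a 10-point risk difference.** The fit gives 62.1% and 72.1% deficient.
- *74 places:* (214.2 + 74 × 0.721)/414 = 64.6%, **+1.6 points**.
- *Extension:* 128/0.721 ≈ 178 more women, about 518 in all; (214.2 + 128)/518 = 66.1%, **+3.1 points**.

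**8. Slight enrichment.** If the HDP share rose from 8% to 13%, the shift is 0.05 × 0.10 = 0.5 points on the risk-difference scale, or 0.05 × (0.776 − 0.617) = 0.8 points on the odds-ratio scale.

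**The case against.** The strongest reply is that this is a conjecture about conduct. Nothing in the article says that women are selected or approached for phase 1 because of HDP, and phase 1 eligibility does not mention blood pressure. That stands: the bias is conditional.

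A reader might infer that enrichment has already occurred, from 22 of 72 phase 2 women (31%) having HDP set beside the Introduction's "Preeclampsia is a complication of 2%-8% of all pregnancies worldwide". The documents do not support this. The 22:50 split could come from taking every case and only some eligible controls. The 2%-8% figure is for preeclampsia worldwide, whereas cases here also include gestational hypertension, eclampsia and HELLP syndrome, at a tertiary hospital. Against phase 1, 22 of 340 is only 6.5%.

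Nor is the 36% floor the share that would deliver the target. At 77.6% deficient, 150 cases need 150/0.776 ≈ 193 women with HDP, about 47% of 414.

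Total Sample Size does not repeat the phase 1 condition, so cases may have been meant to come from outside the 414. If so, and if they are not counted in phase 1, the bias does not arise. This is a fair reading, but it conflicts with the phase 2 participant section, and no separate route is described.

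Removing the 22 cases changes the interim prevalence only from 63% to (214.2 − 22)/(340 − 22) = 60.4%. That is no test of enrichment, because it removes only women already known to be deficient.

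The article concedes that its results may reflect who was recruited, and recruitment-log detail can be left to a fuller document. But whether cases are nested in the prevalence sample is a design rule that the article itself states, in a form that works against Objective 1.

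**Conclusion.** A phase 1 of 414, 150 cases nested in it, and a prevalence sample drawn without regard to HDP cannot all hold. That conclusion rests on the article's own figures. Something has to give: the case target, the nesting, the phase 1 size, or the neutrality of the prevalence sample. The article does not say which, and its two statements on sampling disagree, so neither can be relied on to protect the estimate.

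If the neutrality gives way, the Objective 1 prevalence is biased upward by roughly 1.6 to 2.6 points (remaining places filled with women with HDP) or 3 to 5 points (phase 1 extended to 150 cases), against a stated margin of 5 points. With slight enrichment it is under 1 point. These sizes assume that the 21% versus 11% contrast carries over, as an odds ratio or as a risk difference, and that about 8% to 9% of phase 1 women have HDP so far, inferred from the 22 cases. The article reports no HDP share for phase 1.

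It would go too far to say that the prevalence estimate is biased as it stands. Whether women with HDP were sought out for phase 1 cannot be determined from the article.

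**What to change.** 1. Reconcile Settings, the phase 2 Participants and Data section, Total Sample Size, and Strengths and Limitations, so that they agree on how women are sampled and on whether cases may come from outside the 414.
2. State that women approached because of HDP enter phase 2 by a separate route, with 25(OH)D measured for eligibility, and are not counted in the 414.
3. Define the Objective 1 analysis set, for prevalence and for risk factors, as women sampled regardless of blood pressure.
4. For women already enrolled, record the recruitment route where logs allow, and report prevalence with and without any HDP-targeted recruits.

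The cost is one route variable, a sentence on the analysis set and a short amendment. The downside is a somewhat smaller prevalence denominator if some enrolled women turn out to have been targeted. The change protects the phase 1 estimate; it does not make 150 cases attainable, which remains a question of recruitment time and source.
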